### Measures

Severity of depressive symptoms, measured using the HRSD [42], will be the primary outcome measure of the trial. The HRSD is a 17-item measure administered by clinical interviewers. Depressive symptoms severity is calculated by summing up all 17 items. Secondary outcomes will be assessed using, among others, self-reported symptoms (i.e., BDI [50]; Beck Anxiety Inventory, BAI [53]; Outcome Questionnaire-30, OQ-30 [54]), interpersonal functioning (i.e., Interpersonal Problems Inventory, IIP-32 [55]), and quality of life (Quality of Life Enjoyment and Satisfaction, Q-LES-Q [56]). Process measures will be assessed using the Self-Understanding of Interpersonal Patterns Scale, (SUIP [13]), the Emotion Approach Coping Scale (EACS [57]), the Emotion Regulation Questionnaire (ERQ [58]), the Difficulties in Emotion Regulation Scale (DERS [59]). We will also assess the working alliance (Working Alliance Inventory, WAI [60]), affect (Positive and Negative Affect Scale, PANAS [61]), and therapeutic interventions (Multi-theoretical List of Therapeutic Interventions, MULTI [62]). We will use validated versions of all questionnaires in Hebrew.

### Ethical considerations

The study design, procedure, and informed consent form were approved by the ethics committee of the University of Haifa (approval number: 395/19, Date: 10/30/2019). Any modifications of the protocol will be reported to the committee. As detailed above, participants will be given comprehensive information about the study procedure both orally and in writing. The information describes the possible implications of their participation, including potential risks, inconvenience, and benefits. In the event of a significant adverse incident (e.g., severe suicide risk), the RISK protocol will be activated. Specifically, a special committee including three licensed clinical psychologists trained to deal with such situations will immediately take charge.

### Data management

To warrant confidentiality of the data at all stages of the research process, an elaborated data management plan is deployed. A data monitoring committee will supervise data collection. An identification number will be assigned to each participant on enrollment and will be used for data registration. The correspondence list will be kept securely in a password-protected computer. After completion of the trial, the raw data will be kept in a locked drawer in a locked room at the University of Haifa Psychotherapy Lab. After the dataset is de-identified and anonymized, researchers who will be approved by the steering committee will be able to access the dataset.

### Data analysis and power analysis

Analyses will be conducted on the intention-to-treat sample, using moderated-mediation models. The main analyses will focus on the main outcome measure (HRSD) and on the measures for each of the three mechanisms. Characteristics of the treatment groups will be described at baseline. Insight and emotional processing at baseline will serve as the moderators. We will examine the proposed moderated-mediation model for each mechanism separately, in a series of multilevel models [25]. According to the literature, in the type of analyses we conduct, it is possible to use the level of a measure at baseline as a moderator, and changes in the same measure during treatment as a mediator [26]. Therapist effects will be estimated as random effects in all models.

The sample size was chosen to provide adequate power to test our hypotheses. To estimate the final sample size for the study, we first estimated the required sample size for the first step, predicting the mechanism using Monte Carlo simulations in the R package “powerlmm” [63]. Assuming alpha = 0.05 and a medium effect size (Cohen’s D = 0.6), the simulations indicated a need for a sample size of 120 participants to ensure a power of at least 0.80. Next, using the same approach, we estimated the required sample size for the second step of the proposed moderated-mediation model. Assuming alpha = 0.05 and a medium effect size (Cohen’s D = 0.6) for the association between a mechanism and treatment outcome, the simulations indicated a need for a sample size of 116 participants to ensure a power of at least 0.80. Finally, we calculated the required sample size for the entire moderated-mediation model, using Monte-Carlo simulations and previously assumed effect sizes for each step, resulting in 124 patients.

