What happens when a patient receives a treatment that is based on the patient’s strength as its main mechanism of change? In the example of insight, the patients receive a treatment based on insight, but they may show no or very little change in insight because of an already high level of performance in this area (ceiling effect). Yet, it may still be effective to work on the patient’s strengths, not because of the theory-specific mechanism of change (boosting insight and emotional processing), but because alternative mechanisms may play a role. Promising candidates for such alternative mechanisms are the common mechanisms, which have been shown to contribute to outcome across treatments [34]. The most researched common mechanism is the working alliance between patients and their therapists, generally defined as the emotional bond established in the therapeutic dyad and the agreement between patient and therapists concerning therapy goals and the tasks necessary to achieve them [35–37]. When working on strengths, the therapists may adopt techniques that are less intended to confront the patients with a different way of perceiving and reacting to the world, and more naturally support the patient’s own adaptive patterns of experiencing and reacting. Such supporting work in treatment may help therapists create a strong emotional bond with their patients, who may more readily perceive the therapists as acting for their benefit. Patients may also find it easier to agree with the therapists on the tasks and goals of treatment, which mirror their own assets. Thus, capitalizing on patients’ strengths may bring about therapeutic change through the mechanism of strengthening the alliance.

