## Method

### Study design

The proposed trial aims to investigate the different mechanisms underlying SET vs. EFT, and follows the requirement for an RCT with a design of two parallel groups. Each condition can be considered as a control group for the other [38]. Participants will be allocated into one of two groups, SET and EFT, with an assignment ratio of 1:1. To ensure balance across age, sex, family status, baseline 17-item Hamilton Depression Rating Scale (HRSD), and personality disorders, a minimization algorithm will be used. Only the therapists and their supervisors will be exposed to participant allocation, while the rest of the research team will be blind to the patients’ assignment to treatment. The study protocol follows the Standard Protocol Items: Recommendations for Interventional Trials (SPIRIT) checklist [39].

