### Participants

Participants will be one hundred and twenty-four patients diagnosed with MDD who live in Israel. Recruitment will take place through advertisements, offering free treatment at the University of Haifa Psychotherapy Research Lab clinic (Fig. 2). The sample size was chosen to provide adequate power to test our hypotheses.

**Inclusion criteria:** (a) current MDD based on the Mini International Neuropsychiatric Interview, MINI 7.0.2 (Structured Clinical Interview for DSM5 [40, 41]), and scores above 14 on the 17-item HRSD [42] at two consecutive assessments, one week apart; (b) for participants using psychiatric medication, the dosage must be stable for at least three months before the beginning of the study, and they will be asked to maintain stable dosage during the treatment; (c) age between 18 and 65 years [43]; (d) Hebrew language proficiency; (e) provide written informed consent.

**Exclusion criteria:** (a) current or past schizophrenia or psychosis, bipolar disorder, or severe eating disorder, demanding close medical monitoring; (b) history of organic mental disease; (c) current risk of suicide or self-harm (HRSD suicide item > 2); (d) current substance abuse disorder; (e) being currently in psychotherapy.

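### The total of 124 does not fit the two step sample sizes of 120 and 116 at a common 0.80 target, so the printed figures do not support the claim of adequate power for hypotheses (a) to (d)

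*Protocol article*

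**What the plan says.** The protocol article builds its sample size in three stages under Data analysis and power analysis.

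- Step 1, predicting the mechanism, with Cohen's d = 0.6 and alpha 0.05: "the simulations indicated a need for a sample size of 120 participants to ensure a power of at least 0.80".
- Step 2, linking the mechanism to outcome, with the same alpha and the same d: "the simulations indicated a need for a sample size of 116 participants to ensure a power of at least 0.80".
- The entire moderated-mediation model, "using Monte-Carlo simulations and previously assumed effect sizes for each step, resulting in 124 patients".

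The first two stages carry a power target. The third carries none. The article does make a general claim, under Participants and again in the power section: "The sample size was chosen to provide adequate power to test our hypotheses".

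Each hypothesis in Study hypotheses is a two-link chain within a baseline subgroup: the treatment moves a mechanism (or the alliance) in patients low or high on that mechanism, and that movement improves outcome.

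**The concern.** A chain of two links is detected only if both links are. When each link has power of about 0.80, the chain has clearly less, unless the two tests almost always succeed or fail together. The article adds only 4 patients to the larger step (124 − 120 = 4) and calls the result the requirement for the full model. It does so immediately after two 0.80 targets and with the step effect sizes carried over. A reader will take 124 as giving 0.80 for the hypotheses.

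The mechanism test is the trial's primary objective. If the real power is nearer two in three, about one trial in three would miss a true two-step effect of the assumed size, and a null result would be read as stronger evidence against the theory than it is.

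**Working it through.** **Inputs from the article.** Alpha 0.05 (sidedness not stated; two-sided taken here); d = 0.6 in both steps; 120 and 116 for power of at least 0.80; 124 for the full model; allocation "with an assignment ratio of 1:1".

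**1. Can 120 and 116 be reproduced?** For a plain two-group comparison, n per arm = 2(1.960 + 0.842)² / 0.6² = 43.6, so 44 per arm and 88 in total. Reading step 2 as a correlation, r = 0.6/√(0.36 + 4) = 0.287, which needs about 93. Neither gives 120 or 116. The ratios are 120/88 = 1.36 and 116/88 = 1.32. Design effects of that size, or dropout of about 27% and 24%, would bridge the gap. Since the figures come from simulating multilevel models, the difference is no error; the step sizes can be neither confirmed nor refuted. They are taken at face value below.

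**2. Step power at 124, if 120 and 116 are minima for 0.80.** The standardised effect at the stated size is 1.960 + 0.842 = 2.802, and it grows with √N.

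- Step 1: 2.802 × √(124/120) = 2.848; power = Φ(2.848 − 1.960) = 0.813.
- Step 2: 2.802 × √(124/116) = 2.897; power = Φ(2.897 − 1.960) = 0.826.

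**3. Power for both steps at 124.** With independent step tests, 0.813 × 0.826 = 0.671. For correlated tests (bivariate normal):

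| Correlation | Joint power |
|---|---|
| 0 | 0.67 |
| 0.3 | 0.69 |
| 0.5 | 0.71 |
| 0.8 | 0.75 |
| 0.95 | 0.79 |
| 1 (ceiling) | 0.81 |

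The choice of test does not rescue the figure. With the effects calibrated in this way, simulated power at 124 was 0.64 to 0.68 for a Monte Carlo interval on the product, and about 0.44 for the Sobel test.

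**4. Size needed for a joint 0.80 (independent tests).** At N = 155 the steps have 0.890 and 0.899, product 0.800. At 154 the product is 0.797. With one-sided tests the size is 161.

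**5. What would make 124 right?** A joint 0.80 at 124 with independent tests needs step power of about 0.88 at 120 and 116. But then 0.80 would already be reached at 120 × (2.802/3.135)² ≈ 96 and 116 × (2.802/3.135)² ≈ 93, which does not sit with a stated need for 120 and 116.

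**6. Moderation, as an illustration only.** The printed inputs do not say whether d = 0.6 is an overall or a moderated effect. Suppose it is the effect in one half of an assumed median split (31 per cell) and zero in the other half. This is in the spirit of the Background, which expects that patients already high on insight "they may show no or very little change in insight because of an already high level of performance in this area". The interaction then has standard error 4/√124 = 0.359, z = 0.6/0.359 = 1.67, and power Φ(1.67 − 1.96) = 0.39, before any clustering. With the moderator kept continuous (assumed normal, residual SD 1), the same contrast is a slope of 0.6/1.596 = 0.376 per SD with standard error 2/√124 = 0.180, and power about 0.55. Both are below 0.80, but the size depends on coding that the article does not give.

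**The case against.** **No power is printed beside 124.** This is correct. A reader might infer that the article claims 0.80 for all three sizes and that this is arithmetically impossible. The text does not support that: 0.80 is attached to 120 and 116 only, the wording is at least 0.80, and perfectly correlated step tests would give 0.81. What stands is narrower. The article calls 124 the required size right after two 0.80 targets and claims adequate power; if 124 serves a lower target, it should say so.

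**The shortfall depends on reading 120 and 116 as minima.** Also correct. On a plain unclustered d = 0.6, each step has 0.916 at 124 and the pair about 0.84. But that calculation needs only about 88 to 93 patients per step, so it cannot be what produced 120 and 116, and it leaves out moderation, therapist effects and dropout.

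**Clustering and dropout may already be in the step sizes.** They may, since therapist random effects are planned in all models. A reader might want to cut the 0.67 further for both. With no intraclass correlation, caseload or dropout rate in the article, that would rest on invented inputs and might count the same loss twice.

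**The step effects may already be the moderated ones.** The article describes the steps as parts of the moderated-mediation model, so confining d = 0.6 to half the sample might penalise it twice. For this reason the subgroup figures are illustrations. It would be tempting to conclude that power is below 0.60 for every hypothesis, or that a null result is as likely as not; both come from an assumed split. On the printed step figures, the chance of missing a true two-step effect is about one in three.

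**An article may leave simulation detail to the full protocol.** Agreed, and the absent detail is not the point. The point is that the three printed figures do not fit together.

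**Conclusion.** The point holds in conditional form. If 120 and 116 are the minimum sizes for 0.80 per step, 124 gives about 0.67 for an effect that needs both steps, rising to 0.79 at a correlation of 0.95 between the step tests, and 0.80 would need about 155. The article gives no reason to expect near-perfect correlation. So 124 does not fit the step figures at the same target, and the statement of adequate power for hypotheses (a) to (d) is unsupported by what is printed. Power would be lower again if d = 0.6 is an overall effect and not the moderated one, by an amount that the article does not allow one to fix.

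The result assumes two-sided alpha 0.05, step sizes taken at face value, and a full model that needs both steps with the step effect sizes, as the article describes. It does not show that the unseen simulation was wrong.

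**What to change.** Keep 124. Rerun the full-model simulation on the model that will be fitted: treatment by baseline moderator, mechanism to HRSD, therapist random effects, and expected dropout. Say which test of the indirect effect is used and whether d = 0.6 is an overall or a moderated effect. Replace the general statement of adequate power with the power that 124 gives for the conditional indirect effects and for their moderation.

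If the rerun confirms 120 and 116 as minima, state about 0.67 for the two-step effect, conditional on that reading, in place of an implied 0.80. The illustrative subgroup figures above, and any effective sample size built on an assumed intraclass correlation, should not go into the protocol.

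The cost is one rerun of the simulation and probably a less favourable stated power. Recruitment, design and analysis are unchanged.

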### Dissemination policy

Study results will be disseminated to the public at academic conferences and in peer-reviewed journals. The steering committee will determine authorship of the planned primary and secondary publications. The order of the authors will be decided based on the contributions of each member.

## Discussion

MDD is the leading cause of disability worldwide [1]. Several treatments for MDD have been found to be similarly effective and more effective than control conditions, including supportive-expressive treatment [64] and emotion-focused treatment [65]). Yet, about half the patients receiving any treatment for MDD fail to show adequate response. Although there is low variance between distinct psychotherapies for MDD, there is high variance within each psychotherapy condition. Secondary post hoc analyses on RCT datasets suggest that different subgroups of MDD patients respond best to different treatments, highlighting the need for progress toward personalized treatment for MDD [21, 22]. Currently, there are few evidence-based tools to guide clinicians in patient assignment to their optimal treatment.

The present research makes several important contributions: (a) Theoretical contribution to *psychotherapy* research. This is the first study to explore patient-specific mechanisms of change by integrating the two most researched questions in psychotherapy research: why treatment works and for whom. This conceptual convergence can lead to higher-resolution psychotherapy research that better captures the complexity and richness of the process of therapeutic change. (b) Theoretical contribution to *psychopathology* research. Identifying unique mechanisms of change for given subpopulations of patients can advance our understanding of subtypes within MDD diagnosis and isolate the differences between them. It can also help characterize the risks and protective factors of subtypes of MDD and produce subpopulation-specific warning signals before relapse. The potential role of these mechanisms can then be tested in trans-diagnosed populations. (c) Methodological contributions. *First*, the proposed study will contribute to modifying the classical design for investigating mechanisms of change, into one that incorporates the premise that distinct subpopulations of patients may show different potential to benefit from any given mechanism, taking into account expected moderators in addition to mediators. *Second*, when testing the effects of mechanisms on outcome, studies have relied mostly on self-report measures, which depend heavily on the individual’s awareness, ability, and motivation to report on such processes. The present study uses interdisciplinary measures based on hormonal and acoustic measures, clinician interviews, and behavioral coding systems to complement the self-report measures. (d) Clinical contribution. The research on personalized mechanisms of change can help clinicians avoid unnecessary or irrelevant therapeutic elements, and focus on more efficient treatment delivery, adapted to given subpopulations of patients, according to their strengths and weaknesses. If a mechanism most likely to stimulate change for a subpopulation is identified, a corresponding treatment can be chosen that is most likely to activate that particular mechanism.

### Trial status

At the time of submission, recruitment status was pending: no participants are being recruited or enrolled yet. The anticipated date of enrolment of the first patient is November 2020. The recruitment phase of the trial is anticipated to be completed by end of 2026.

## Data Availability

Data sharing is not applicable to this article as no datasets were generated or analysed during the current study.

## Abbreviations

BAI: Beck anxiety inventory
BDI: Beck depression inventory
DERS: Difficulties in Emotion Regulation Scale
EFT: Emotion Focused Therapy
EACS: Emotion Approach Coping Scale
ERQ: Emotion Regulation Questionnaire
HRSD: Hamilton rating scale for depression
IIP: Inventory of interpersonal problems
MDD: Major depressive disorder
MINI: Mini International Neuropsychiatric Interview
MULTI: Multi-theoretical list of therapeutic interventions
OQ: Outcome questionnaire
PACS: Penn adherence-competence scale
PSQ: Post-session questionnaire
PANAS: Positive and Negative Affect Scale
PCEPS: Person-Centered and Experiential Psychotherapy Scale
Q-LES-S-: Quality of Life Enjoyment and Satisfaction Questionnaire
RCT: Randomized controlled trial
SE: Supportive-expressive
SIDP: Structured interview for DSM-IV personality
WAI: Working alliance inventory
